**Fig. 3 Fig3:**
[figure not shown]
Possible outcomes of the PRECiSE non-inferiority RCT. The non-inferiority margin is set to a 10% absolute difference in live birth rate, which corresponds to a risk ratio (RR) of 0.6 for p.f.d 5 versus p.f.d.3 embryo transfer. **a** the lower bound of the confidence interval (CI) lies above the non-inferiority margin of 0.6: p.f.d. 5 is non-inferior to p.f.d. 3 embryo transfer (**b**) the lower bound of the CI lies above the non-inferiority margin and the CI includes the null value (RR = 1.0): p.f.d. 5 is non-inferior and equivalent to p.f.d. 3 embryo transfer (**c**) and (**d**) the CI includes the non-inferiority margin of 0.6: inconclusive (**e**) the upper bound of the CI lies below the non-inferiority margin of 0.6: p.f.d. 5 is inferior to p.f.d. 3 embryo transfer (**f**) the lower bound of the CI lies above the null value (RR = 1.0): p.f.d. 5 is superior to p.f.d. 3 embryo transfer

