### Randomization

Embryos will be assessed on day 1 following egg retrieval, in accordance with usual clinical practice. If patients have 1 to ≤5 embryos with 2 pronuclei available, they will be randomized to receive a cleavage- or blastocyst -stage embryo transfer. We will use computer-generated block randomization to randomize participants in a 1:1 ratio to the day 3 or day 5 treatment arm. Randomization will be stratified based on treatment center, age (< 38 and ≥ 38 years) and by embryo number (1–2 and 3–5 embryos on day 1 after egg retrieval). Randomization will be performed electronically using a secure web application (REDCap). Allocation concealment will be ensured, as randomization will not occur until the patient becomes eligible to participate in the trial, which takes place after consent to participate. In addition, randomization will be performed by embryology lab personnel and not recruiting study physicians. As per standard clinical practice, a clinician (who also is a member of the study team) will call participants to inform them of the number of fertilized embryos and, at this point, will also inform them of the day of transfer to which they have been randomized. At this point, participants will have an opportunity to not continue with the day of transfer to which they were randomized. We anticipate that most of the crossovers will occur due to participants in the p.f.d. 5 group with only 1–2 embryos wishing to have an embryo transfer on p.f.d. 3. Participants who choose to not continue with their assigned day of transfer will be asked to continue their participation so that we can collect cycle outcome data for the intention-to-treat analysis. Due to the nature of the intervention neither participants nor staff can be blinded to allocation, but are strongly inculcated not to disclose the allocation status of the participant at the follow up assessments. An employee at Boston IVF outside the research team will feed data into the computer in separate datasheets so that the researchers can analyze data without having access to information about the allocation. Trial conduct and protocol adherence will be audited every 6 months by the clinical director of each individual study site.

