Our choice of a non-inferiority margin, i.e. the largest clinical difference in the live birth rate per retrieval that is acceptable between cleavage- and blastocyst-stage embryo transfer, is based on a combination of clinical judgment and statistical reasoning. Given that there are no data from previous trials to help define the clinical difference between cleavage-stage and blastocyst transfers in poorer prognosis patients, we have relied on our own and outside experts’ clinical judgment to determine that a non-inferiority margin of 10% is clinically acceptable. We used data from Boston IVF to estimate the live birth rate per transfer for cleavage-stage embryos. Among women with ≤5 zygotes on day 1, approximately 24% achieved a live birth after a day 3 transfer. Given that many of these cycles will not result in cryopreservation of embryos and subsequent frozen embryo transfer, it is reasonable to assume a live birth rate per cycle of approximately 25% for p.f.d. 3 transfers. Assuming a 25% live birth rate in both groups, a non-inferiority margin of 10%, a one-sided significance level of 0.025, and 80% power, a sample size of 296 per group is required. To allow for up to 10% of patients to withdraw from the study after randomization or be lost to follow-up, we aim to enroll 329 participants per group, yielding a total sample size of 658 participants. We estimate that there were 710 eligible patients in 2018 across all sites. Assuming 50% of eligible patients will consent to study participation, we anticipate an enrollment period of 22 months. Given that patients store their frozen embryos at our facilities we expect minimal loss to follow-up.

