Both intention-to-treat and per-protocol analyses are noted in the RCT reporting guidelines (CONSORT) as valid approaches. For this study, we will perform an intention-to-treat analysis because it is the gold standard for RCTs, even with crossover, withdraw and loss to follow-up. We also will perform a per-protocol analysis as it is a valid statistical approach and will serve as a sensitivity analysis. Descriptive data will be presented as proportion, mean with standard deviation or median with interquartile range. Comparisons will be made using Chi-square or Fisher’s exact tests for categorical variables and parametric or non-parametric tests for continuous variables based on data distribution. We will use log-binomial regression to estimate risk ratios (RR) and 95% confidence intervals for the primary and secondary outcomes. While we anticipate that randomization will balance the distribution of measured and unmeasured potential confounders in the two study arms, if this is not the case, we will assess the influence of potential confounders as needed. In addition, we will perform pre-specified subgroup analysis among participants with ≤2 versus 3–5 zygotes on p.f.d 1, as well as participants with poor versus good quality embryos undergoing single embryo transfer. We will base analyses of the heterogeneity of treatment effects for these subgroups on a statistical test for interaction [18, 19]. This interaction test examines the extent to which any observed difference across subgroups may be attributed to chance variation. All data will be analyzed with SAS 9.4 (SAS Institute Inc., Cary, NC, USA).

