The primary outcome of the trial is the live birth rate (≥ 22 weeks of gestation) per retrieval among poorer prognosis participants who have a cleavage stage embryo transfer compared with a blastocyst transfer in an intent-to-treat analysis. The intention-to-treat population will include all randomized participants, including those who cross over to the other treatment group (i.e. participants who are randomized to the blastocyst transfer group but in fact receive a cleavage-stage embryo transfer or participants in the cleavage-stage group who request a blastocyst transfer). Assuming a 25% live birth rate for cleavage stage transfer, a 10% absolute difference in live birth rate between blastocyst and cleavage-stage embryo transfer corresponds to a RR of 0.6 (RR = 0.15/0.25) (Fig. 3). The primary analyses will therefore be interpreted as follows: If the lower bound of the 95% confidence interval (CI) for the difference in live birth rates per retrieval lies to the right of the 10% non-inferiority margin (RR = 0.6), we will have proven non-inferiority of blastocyst transfers at the level of significance α = 0.025; superiority will be demonstrated if the lower bound of the two-sided 95% CI lies fully to the right of 1.0. If the whole 95% CI lies below the non-inferiority margin (RR = 0.6) for the outcome difference the treatment group will be declared “inferior.” If the 95% CI includes the RR = 0.6 noninferiority margin the study results will be deemed inconclusive (Fig. 3) [20].

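### The Fig. 3 rules call a non-significant result equivalence without an upper limit, and give a significantly lower live birth rate no conclusion of its own

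*Protocol article*

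**What the plan says.** The section on data collection and statistical analysis sets out how the primary result will be read, and the Fig. 3 legend repeats it as cases (a) to (f). The margin is 10 percentage points, expressed as RR 0.6 at a 25% cleavage-stage rate. The rules are:

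- **Non-inferior:** lower 95% limit above 0.6.
- **Superior:** lower limit above 1.0.
- **Inferior:** whole interval below 0.6.
- **Inconclusive:** "If the 95% CI includes the RR = 0.6 noninferiority margin the study results will be deemed inconclusive". The legend gives cases (c) and (d) this same label.
- **Case (b), legend only:** lower limit above 0.6 and interval including 1.0, with the conclusion "p.f.d. 5 is non-inferior and equivalent to p.f.d. 3 embryo transfer".

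The analysis section itself does not use the word equivalent. Neither place states how high the upper limit may go before equivalence is ruled out.

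**The concern.** There are two separate problems.

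First, equivalence is a two-sided claim and needs the whole interval inside a lower and an upper bound. Case (b) has only the lower one. An interval that includes 1.0 shows only that no difference was demonstrated. A result compatible with a blastocyst gain larger than the trial's own margin would still be called equivalent.

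Second, a significant gain has its own label as soon as the interval excludes 1.0. A significant loss has none unless the interval also excludes 0.6. An interval that contains 0.6 and lies wholly below 1.0 shows fewer live births with blastocyst transfer, yet the only prescribed conclusion is that the study is inconclusive.

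The Discussion says the trial may lead to routine blastocyst culture for all patients, so the wording attached to results in these two zones matters.

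**Working it through.** **Inputs.** The sample size section gives the planning values: "Assuming a 25% live birth rate in both groups, a non-inferiority margin of 10%, a one-sided significance level of 0.025, and 80% power". It arrives at 296 per arm, adds a 10% allowance for withdrawal and loss, and ends at 329 per arm (658 in all). Allocation is 1:1 according to the randomization section. The effect measure comes from the analysis section: "We will use log-binomial regression to estimate risk ratios (RR) and 95% confidence intervals". True blastocyst rates other than 25% are my assumptions.

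**The plan's own figure.** n = (1.960 + 0.842)² × (0.25×0.75 + 0.25×0.75) / 0.10² = 7.849 × 0.375 / 0.01 = 294.3, so 295 per group against the stated 296. Then 296/0.90 = 328.9, so 329 per group and 658 in total. The plan's numbers reproduce.

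**Intervals.** For x₁ blastocyst and x₀ cleavage births out of n per arm:

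- RR interval: exp[ln(x₁/x₀) ± 1.96·√(1/x₁ + 1/x₀ − 2/n)]
- Difference interval: (p₁ − p₀) ± 1.96·√[p₁(1−p₁)/n + p₀(1−p₀)/n]

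**Zones at 296 per arm with 74 cleavage births (25%), using the RR interval:**

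| Blastocyst births | Conclusion under the rules |
|---|---|
| 29 or fewer | inferior |
| 30 to 54 | inconclusive, interval wholly below 1.0 |
| 55 to 59 | inconclusive, interval includes 1.0 |
| 60 to 95 | non-inferior and equivalent |
| 96 or more | superior |

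**Example for case (b).** 95 against 74 births (32.1% against 25.0%):

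- RR = 1.28; SE of ln RR = √(1/95 + 1/74 − 2/296) = 0.131; interval 0.99 to 1.66.
- Difference = +7.1 points; SE = 3.7 points; interval −0.2 to +14.3.

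The rules call this equivalent.

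**Example for the inconclusive label.** 52 against 74 births (17.6% against 25.0%):

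- RR = 0.70; SE of ln RR = √(1/52 + 1/74 − 2/296) = 0.161; interval 0.51 to 0.96.

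The rules call this inconclusive, although the interval excludes 1.0.

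**How often.** Exact enumeration of two binomials, cleavage rate 25%, labels taken from the RR interval. The third column uses the upper limit of the difference interval. All columns are shares of all trials at 296 per arm.

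| True blastocyst rate | Case (b) label | Case (b) label and upper limit beyond +10 points | Inconclusive with interval wholly below 1.0 |
|---|---|---|---|
| 15% | 3% | 0% | 84% |
| 20% | 47% | 1% | 30% |
| 25% | 92% | 17% | 2% |
| 30% | 73% | 45% | 0% |

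Taking the label from the difference interval as well gives 17% and 44% (17.1% and 44.5% before rounding) in the third column at 25% and 30%, so mixing the scales does not drive the result. With 329 per arm the picture is similar: 87% at a true 15% in the last column, and 40% at a true 30% in the third.

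**The case against.** *Inconclusive* is a coherent answer to the question the trial asks. The primary aim is non-inferiority at a margin defined as the largest acceptable loss. An interval straddling 0.6 cannot say whether the loss exceeds it, and the label never licenses adopting blastocyst transfer. This stands. What it does not cover is that the rule applies the label to the study results as a whole and offers no second statement for an interval that excludes 1.0.

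A reader might infer that significant harm would be hidden or misreported. The documents do not support that. The analysis section commits to reporting RRs with 95% intervals for the primary outcome, so an interval such as 0.51 to 0.96 would be visible, and nothing forbids saying that it excludes 1.0.

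A reader might also cite the fact that, at a true 15% against 25%, 95% of trials are inconclusive and only 2% inferior. That is no evidence of a faulty rule. With the truth placed on the margin, a 95% interval contains the margin about 95% of the time at any sample size.

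*Equivalent* is one word in a legend, no decision depends on it, and every case (b) result does meet the non-inferiority criterion. This is also true. The word is still a stated conclusion that the rule cannot support, and its error would be to understate a possible blastocyst benefit.

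Finally, the figure itself is not shown, and cases (c) and (d) may differ in whether the interval crosses 1.0. Even so, the legend gives them one label.

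**Conclusion.** Both points hold as defects in the stated conclusions. The non-inferiority decision, alpha and sample size are unaffected.

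The equivalence label has no upper limit behind it. At the planning rates about 17% of trials would carry it with an upper difference limit beyond +10 points, and about 45% if the true blastocyst rate were 30%.

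The gap in the inconclusive rule depends strongly on the truth: about 84% at 15% against 25%, 30% at 20% against 25%, and 2% under the planning assumption. It is an incomplete conclusion, not a wrong non-inferiority decision.

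These figures assume 296 analysed per arm, a 25% cleavage-stage rate, unadjusted Wald intervals, and true blastocyst rates that the protocol does not give except for 25%. Using +10 points as a yardstick for the upper limit borrows the trial's own margin for illustration; the protocol sets no upper limit.

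**What to change.** 1. In case (b) of the Fig. 3 legend, delete the equivalence claim so that the conclusion reads: non-inferior, superiority not shown.
2. In the analysis section and in cases (c) and (d), state that if the interval includes the margin and its upper limit is below RR 1.0 (difference 0), the conclusion is: non-inferiority not shown; live birth rate significantly lower with blastocyst transfer.
3. Keep *inconclusive* for intervals that contain both the margin and 1.0. With 74 cleavage births of 296, that leaves 55 to 59 blastocyst births under this label.

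I would not rescue the word *equivalent* by adding a ±10-point bound. That would be a new choice the protocol never made. At 296 per arm and 25%/25% it would be met only about 60% of the time: SE = √(2×0.1875/296) = 3.56 points, 10/3.56 = 2.81, and 2Φ(2.81 − 1.96) − 1 = 0.60.

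The cost is a wording change in two places, with no added patients or analyses.

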### Interim data analysis

A Data Safety and Monitoring Board (DSMB) with no direct involvement in the trial will be appointed. The DSMB is independent of the study organizers at Boston IVF and Clinica Eugin and is chaired by [name] (Beth Israel Deaconess Medical Center). During the period of recruitment to the study, interim analyses will be supplied, in strict confidence, to the DSMB, together with any other analyses that the committee may request. The role of the DSMB will be to deal with any ethical issues that may arise while the trial is in progress and to review the interim analysis. An interim analysis of clinical pregnancy rates will be conducted and reviewed by the DSMB after 50% of the study participants have been randomized.

### Stopping the trial

The DSMB will be asked to give advice regarding stopping the trial if they have evidence of a meaningful advantage or disadvantage for one of the treatment groups and they consider that the results are likely to affect clinical practice. The following guidelines are proposed for the DSMB to recommend stopping the trial or temporarily suspending recruitment if any of the following are observed at the time of the interim analysis: (1) the difference in clinical pregnancy rate exceeds 20% in one fresh transfer group compared with the other; a difference between the two groups will be considered significant if the *p* value for the difference is less than 0.001 (2) there are notably more adverse events, such as miscarriage or multiple pregnancy, in one ET group compared with the other (3) recruitment is not proceeding at rates that will allow the study to reach its target sample size in a reasonable timeframe. It should be noted that if there appears to be an unexpectedly high number of cancelled fresh embryo transfers in the day 5 transfer group, any one of the study institutional review boards may also temporarily or permanently halt the study at any time. If the study is stopped temporarily or permanently for any reason, follow-up of participants already enrolled will continue as originally scheduled and all participants already enrolled will receive continued care, appropriate to their clinical condition and circumstances, in line with each site’s standard practice.

### Duration of project

It is anticipated that the trial recruitment and all follow-up can be completed in approximately 31 months. Recruitment will begin in January 2020 after trial procedures have been tested, study staff trained and materials distributed to all study sites within the Boston IVF and Clinica Eugin networks.

## Discussion

The PRECiSE trial aims to determine whether transfer of cleavage stage embryos in patients with ≤5 available embryos results in similar pregnancy outcomes compared to the culture of all embryos to p.f.d. 5 in vitro followed by blastocyst transfer. In addition, we will evaluate potential negative consequences of cleavage stage embryo transfer (miscarriage and multiple pregnancy) and blastocyst transfer (cycle cancellation). The need for this RCT is clear, because previous trials have not assessed pregnancy outcomes in poorer prognosis patients and cleavage stage embryo transfer is routinely performed in this subgroup at many IVF centers. The PRECiSE trial differs from previous trials in that it will report rates of live birth *per retrieval* together with the incidence of adverse events such as miscarriage and multiple pregnancies.

This pragmatic trial replaces a clinical decision based on empiric physician preference and experience and as a result does not interfere with the logistics of routine IVF care. However, the main challenge for this trial is the relatively low number of patients with ≤5 zygotes on day 1 after fertilization. This is overcome by the large numbers of IVF cycles per year at the participating IVF centers and the inclusion of national and international satellite offices within our network. While patient populations across study sites may vary, stimulation protocols, embryo culture protocols and pregnancy rates are comparable, making the findings generalizable. Another challenge of this study is the possible higher dropout rate for patients with only 1–2 embryos on p.f.d. 1. This is mainly driven by the concern for ‘having nothing to transfer’. This will be partially mitigated by detailed counseling of patients in this group about the absence of evidence for benefit either way.

If the interim analysis indicates a difference in pregnancy rates per retrieval above the 10% inferiority margin we will change the design of the study to a superiority RCT. If no clinically significant differences in pregnancy rates and secondary outcomes are identified, this trial will have important implications for the clinical practice of IVF and may facilitate the adoption of routine blastocyst culture for all patients. This could result in simplified laboratory protocols and reduced costs, as well as higher rates of single embryo transfers and potentially a reduced incidence of multiples and miscarriage.

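### The Discussion commits the trial to switch from non-inferiority to superiority on an interim pregnancy difference above 10 points; the interim and stopping sections do not mention this rule, and the final analysis does not need it

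*Protocol article*

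**What the plan says.** All references are to the protocol article.

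- **Discussion.** "If the interim analysis indicates a difference in pregnancy rates per retrieval above the 10% inferiority margin we will change the design". The sentence goes on to name a superiority trial as the new design.
- **Interim data analysis.** One look is planned, on clinical pregnancy rates, once half the participants are randomised. The section says that "interim analyses will be supplied, in strict confidence, to the DSMB". It does not mention a change of design.
- **Stopping the trial.** The DSMB guidelines for stopping or suspending recruitment cover three situations: a large difference in pregnancy, an excess of adverse events, and slow recruitment. The first applies if "the difference in clinical pregnancy rate exceeds 20% in one fresh transfer group compared with the other", with significance judged at p below 0.001. No switch is mentioned here either.
- **Rationale for the non-inferiority hypothesis and for sample size estimation.** The 10% margin is defined for live birth per retrieval. The design uses "a non-inferiority margin of 10%, a one-sided significance level of 0.025, and 80% power".
- **Data collection and statistical analysis.** The final 95% confidence interval is read as non-inferior, superior, inferior or inconclusive. For superiority: "superiority will be demonstrated if the lower bound of the two-sided 95% CI lies fully to the right of 1.0".

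**The concern.** The sentence makes the primary hypothesis depend on an interim estimate, and four things about it are unsatisfactory.

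1. **Endpoint.** The margin was justified by clinical judgement for live birth per retrieval. The interim concerns clinical pregnancy, which is a secondary outcome. Nothing in the article supports carrying the 10 points over.
2. **Trigger.** It is a point estimate with no significance requirement. The direction is unclear: the phrase about the inferiority margin suggests blastocyst doing worse, while a move to superiority suggests blastocyst doing better.
3. **Fit with the interim sections.** Those sections give the DSMB a confidential look and a list of stopping guidelines. They do not say who would make the switch, or what happens when a difference above 20 points meets both rules. Neither participants nor staff are blinded (Randomization), and women may decline their assigned transfer day. Announcing a switch would tell everyone, at half enrolment, that the arms differ by more than 10 points.
4. **Need.** Superiority can already be claimed at the end from the planned interval, so the switch gains nothing.

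At stake is whether the non-inferiority question is still the one answered when the trial reports. If it is dropped after the switch, a trial that would have met it can end as a failed superiority trial.

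**Working it through.** **1. The plan's own sample size.** Inputs: 25% live birth in both arms, margin 10 points, one-sided 0.025, power 80%.

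n per arm = (1.960 + 0.842)² × 2 × 0.25 × 0.75 / 0.10² = 294.3, rounded up to 295. The article gives 296, which agrees within rounding. Allowing for 10% attrition, 296 / 0.9 = 328.9, so 329 per arm and 658 in total, as stated.

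**2. Size of the interim.** Half of 658 is 329 women, about 164 per arm.

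**3. Chance of crossing 10 points with no true difference.** The article gives no clinical pregnancy rate, so 25% to 40% is assumed. SE = √(2p(1−p)/164), z = 0.10/SE, and the probability is two-sided.

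| Pregnancy rate, both arms | SE (points) | z | P(difference beyond 10 points, either way) |
|---|---|---|---|
| 25% | 4.78 | 2.09 | 3.7% |
| 30% | 5.06 | 1.98 | 4.8% |
| 35% | 5.27 | 1.90 | 5.8% |
| 40% | 5.41 | 1.85 | 6.5% |

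With a true 5-point difference in pregnancy the trigger fires in about 14% to 18% of trials. With a true 10-point difference it fires in 50%.

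**4. Strength of evidence at each threshold.** An observed 25% versus 35% at 164 per arm gives z = 1.98 and p = 0.048; 40% versus 50% gives z = 1.82 and p = 0.069. An observed 20-point difference gives p of about 0.0001 to 0.0003 over the same range. The switch therefore acts on evidence near the nominal 5% level, while the stopping guideline asks for p below 0.001.

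**5. What a switch could cost.** Simulation of 1,000,000 trials per row, with 164 per arm at the interim and 329 per arm at the end. Control live birth is 25%, and live births are drawn from clinical pregnancies at an assumed 70%, 80% or 90%. The final reading is a 95% interval for the risk difference, compared with −10 points (non-inferiority) and 0 (superiority). The lost column counts trials that switch, meet non-inferiority and fail superiority, as a share of all trials, if superiority replaces non-inferiority.

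| True difference in live birth, blastocyst minus cleavage | Pregnancies ending in live birth | Switch (two-directional) | Lost (two-directional) | Lost if only blastocyst-worse differences trigger |
|---|---|---|---|---|
| 0 | 70% | 5.7% | 3.4% | 1.1% |
| 0 | 80% | 4.9% | 2.6% | 0.7% |
| 0 | 90% | 4.2% | 1.9% | 0.5% |
| +5 points | 70% | 29.5% | 13.3% | under 0.1% |
| +5 points | 80% | 23.3% | 8.9% | under 0.1% |
| +5 points | 90% | 18.8% | 5.8% | under 0.1% |

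If the four-way reading in Data collection and statistical analysis is kept after the switch, the lost column is zero in every row. With no true difference, blastocyst is then falsely declared superior in 2.5% of trials, as designed.

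**The case against.** The strongest reply is that the sentence does less than it seems to.

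- **No contradiction with the stopping guidelines.** A reader might infer that the 10-point and 20-point rules contradict each other. They do not: one changes the design and the other advises stopping or suspending recruitment, and at 12 points both can be followed. The differing descriptions of the measure (fresh transfer groups versus per retrieval) may only be two ways of naming the randomised arms. What stands is that the rules are unreconciled.
- **Non-inferiority may survive the switch.** A reader might infer that the test is discarded. That is a natural reading of changing the design, but the article does not say so, and the final reading covers both conclusions. The losses above are conditional on the test being dropped.
- **Direction.** If only blastocyst-worse differences count, the loss in the +5 scenario almost disappears. Any harm in that branch would come mainly from someone misreading a non-significant superiority test as no difference, and I do not count it.
- **Blinding of the interim.** The article never calls the interim unblinded. That follows only because a difference between arms needs data by arm.
- **Condensed article.** Direction, decision maker and error control may be set out in a fuller document, so their absence weighs little. The commitment itself, its endpoint and its mismatch with the other sections are stated in the text shown.

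**Conclusion.** The concern holds as a defect of design and consistency. The article commits to changing the primary hypothesis on an interim pregnancy estimate, using a margin set for another endpoint. The rule has no place in its own interim and stopping sections, would disclose a confidential result, and serves a purpose the final analysis already meets.

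The trigger fires by chance in 3.7% to 6.5% of trials without a true difference, for assumed pregnancy rates of 25% to 40%. The loss of non-inferiority conclusions is about 2% to 3% of all trials under the plan's own equal-rates assumption. It is about 6% to 13% if blastocyst is truly 5 points better on live birth. Both ranges require a two-directional trigger, replacement of the non-inferiority test, 25% control live birth and 70% to 90% of pregnancies ending in live birth. If the planned final reading is kept, nothing is lost.

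A reader might also infer an inflated false-positive rate. The documents do not support that: with the sample size and final tests unchanged, false blastocyst superiority stays at 2.5%. Inflation could come only from a redesign that the article does not describe.

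**What to change.** Delete the design-switch sentence from the Discussion. In its place, or in Interim data analysis, state three things:

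- The non-inferiority hypothesis, the margin and the primary analysis on live birth per retrieval stay fixed whatever the interim shows.
- Superiority is read at the end from the same confidence interval, as Data collection and statistical analysis already provides.
- Action at the interim is limited to the DSMB guidelines already listed under Stopping the trial.

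The cost is one sentence removed and a short statement added, with no extra patients and no loss of power. It should be settled before the look at 50% randomisation, because a later change would itself appear data-driven.
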